### Inclusion criteria

Age eighteen years or older.

French speaking.

French social security affiliation.

Ability and willingness to participate in all the assessments, with written consent to the protocol.

Poorer ear: severe-to-profound hearing loss measured using pure tone audiometry with pure-tone average (0.5, 1, 2, 4 kHz) ≥ 70 dB, confirmed by auditory brainstem responses, with minimal benefit of a conventional hearing aid. In order to account for the heterogeneity of this population, no selection was applied on the duration of deafness or the severity of the tinnitus.

Better ear: normal hearing thresholds (≤20 dB HL) to moderate hearing loss (PTA ≤ 60 dB HL).

### Exclusion criteria

Retrocochlear pathology (vestibular schwannoma, severe central auditory processing disorder).

Major cochlear ossification or malformation which could prevent the full insertion of a cochlear implant, controlled on CT scan and MRI of temporal bones.

Subjects under juridical protections or tutelage measure.

Neurological or psychiatric disorder.

Previous treatment with CROS, BC or CI.

Medical condition that contraindicates CI surgery.

### Randomisation procedure

Randomisation of CI versus observation was based on a 1:1 ratio and was stratified per centre. The allocation sequence was randomly generated by a computer (Stata SE 11.2, ralloc procedure), providing a sequence of treatments randomly permuted in blocks of varying size [2, 4, 6]. There was no blinding procedure in this open-label trial; however randomisation was centralised at the Toulouse University Hospital and managed by the project manager and clinical research associates. The allocation sequence was unknown to the investigators who enrolled participants.

### Population and sample size

The sample size was calculated based on the expected number of failures of CROS hearing aids, BC trials and on the expected improvement of quality of life in cochlear implanted subjects with SSD/AHL. In a pilot study performed in our centre (unpublished), 40 to 50% of SSD/AHL subjects declined both CROS and BC devices after a three-week trial. This rate is consistent with previous studies performed on BC implantation after a headband trial (45% in Desmet et al. [33]). An improvement in quality of life is expected in these subjects after cochlear implantation, but it is not as significant as in patients with bilateral severe-to-profound deafness. A recent meta-analysis performed on traditional CI candidates with severe-to-profound deafness demonstrated an improvement of 1.05 standard deviations. To detect an improvement of 0.8 standard deviations with an alpha risk of 5% and an 80% power, 50 subjects (25 per arm) are necessary. Altogether, and to compensate the risk of dropouts, 150 subjects are included in this study.

### Interventions

The purpose of this study is to assess the cost-utility ratio of CI in subjects with SSD/AHL after failure of more conventional treatments. Therefore, every subject will successively try CROS hearing aids and a BC device placed on a headband, for three weeks each. The baseline assessment of each trial relies on auditory measures (speech recognition in noise and horizontal localisation) and quality of life questionnaires. Once each trial has been performed, the subject will decide which treatment he/she opts for. This choice is mainly based on the subjective feelings of the subject after the two trials, but also guided by the auditory outcomes obtained with each device, and the counselling of the physician. The programme provides all costs directly related to the treatment, i.e. the cost of the medical device and the following fitting sessions.

The information regarding the results which may be expected from a cochlear implant is critical. A CI is the only device which cannot be herein tried before the decision is made and its choice intrinsically relies on hedging a bet. Across the seven centres, this information is standardised through several elements indicated to the subjects willing to try a CI, based on the literature on cochlear implantation outcomes in SSD/AHL [28, 29, 34, 35]:CI may restore binaural hearing to some extent but with a significant inter-individual variability;its effect is more consistent on ipsilateral tinnitus when associated with unilateral profound deafness;The impact of CI in this indication has mainly been studied and demonstrated in subjects where the duration of profound deafness was less than 10 years.

Once this information has been delivered, each subject makes a final choice among four options: abstention, CROS hearing aids, Bone-Anchored hearing aid (Baha or Ponto), or CI. Subjects who chose CI are randomised between two arms (“CI” arm versus “observation” arm) and re-assessed and compared after 6 months their choice has been implemented, and the results of the two arms are compared. Subjects who chose abstention, CROS or BAHA are re-assessed 6 months after their choice has been implemented, and the results of each group are described.

### Abstention

Subjects in this group who do not experience any benefit from the CROS hearing aid trial or from the BAHA trial, and choose no specific treatment for SSD/AHL.

### CROS hearing aids

In CROS systems, a remote microphone which is placed on the poorer ear receives the surrounding incoming signal and transmits it to the second hearing aid on the better ear, using a wireless link. The second hearing aid delivers the signal using air conduction and can also apply an additional amplification in case of hearing loss in the better ear.

A Phonak CROS system will be used for the trials and in case the subject eventually opts for this type of rehabilitation (Phonak AG, Stäfa, Switzerland). The hearing aids will be fitted by an experienced audiologist, using the fitting software provided by the company (Phonak Target™ 3.0).

### Bone conduction device (BAHA)

Bone-anchored hearing aids transmit the auditory signal received by the processor placed behind the poor ear to the better ear through bone conduction of the skull. The programme does not provide any additional hearing aid in the better ear if the subject has AHL.

Baha BP 110® (Cochlear Ltd) and Ponto® (Oticon) will be used on a headband for the trial period and placed on the corresponding abutment after a surgical procedure if the subject chooses this option. The surgery consists of the placement of the implant which aims at being osteo-integrated, on which an abutment is screwed. The processor may be used for 3 to 6 weeks following the surgery according to wound healing. It is then fitted by an experienced audiologist following the company’s guidelines.

### Cochlear implant

A surgical procedure is performed to allow the placement of the receptor under the temporal muscle and the introduction of the electrode array into the scala tympani via the round window or a cochleostomy. According to the company, the electrode array supports 12 to 22 intra-cochlear electrodes which aim at stimulating the first neurons of the auditory nerve. Four cochlear implant companies are involved in this study: Advanced Bionics, Cochlear, MedEl and Oticon. The choice of the brand will depend on the physician in charge of the patient. Approximately four weeks after surgery, the external processor can be activated and the patient will therefore receive electric auditory stimulation of the implanted ear.

### Primary outcome measure

The primary outcome measure will be applied to the two randomised arms to determine the incremental cost-utility ratio (ICUR) of cochlear implantation versus initial observation at 6 months. The utility is defined in this study as survival weighted by the quality of life of patients at 6 months (QALY). Quality of life will be measured using a generic questionnaire, the EuroQol-5D-3 L scale. This instrument is recommended by the national French agency (Haute Autorité de Santé) for cost-utility studies [36].

The EQ-5D-3 L is a self-administered, generic and multidimensional questionnaire [37]. It has two components, a descriptive component and a visual analogue scale (EQ-VAS). The descriptive component is composed of 5 dimensions described by three levels that define 243 health states. The EQ-5D-3 L is translated and validated into the French language and it has a utility function calculated on the basis of known preferences of the French population [38]. The utility-preference approach of the EQ-5D-3 L provides a cardinal measuring instrument available to calculate the cost-utility ratios.

Healthcare costs will be assessed from the French health insurance perspective [39, 40]. Direct medical and non-medical costs will be included in this study. Costs related to productivity loss will also be analysed. Direct medical costs correspond to hospitalisation costs, outpatient costs (i.e. visits and medical acts, paramedical acts), medication and medical device costs, especially the cost of the CI. Non-medical costs include transportation costs. Data linked to the number of days the patient has missed work will also be gathered from the French health insurance databases. Costs will be estimated by multiplying the number of units used for each resource with the corresponding unit cost.

Consumption of healthcare resources will be retrospectively gathered from the French Social Health Insurance databases, using a bottom-up approach. Administrative data corresponding to the name, surname, date of birth, place of living and gender were recorded for patients included in the study.

Inpatient stays will be valued using the French Disease Related Groups (DRGs). Outpatient care, which includes visits, medical and paramedical acts, will be valued using the tariffs reimbursed by the French health insurance. Visits and paramedical acts will be valued using the French General Nomenclature of Professional Acts. Medical acts will be valued using the French Common Classification of Medical Acts, except for laboratory tests for which valuation will be based on the Nomenclature of Biological Acts. For all these fees, we will apply the corresponding reimbursement rate and we will subtract, if necessary, the medical deductible that is due by the patient and not reimbursed by the French Social Health Insurance (FSHI).

A cost-utility analysis will be performed. This study will establish a link between costs and medical consequences, expressed in QALY gained, at 6 months between the two care management strategies. The ICUR between SSD/AHL patients treated by CI and those that are only followed-up, will be calculated as follows (Drummond et al., 2005):$$ ICUR=\frac{\Delta  C}{\Delta  U}=\frac{Mean\ cost\ \left(\  CI\right)- Mean\ cost\ (abstention)}{Mean\ QALY\ (CI)- Mean\ QALY\ (abstention)} $$

Where ΔC and ΔU were increments of costs and utilities, respectively.

A Budget Impact Analysis (BIA) will be implemented to measure the net costs to the social health insurance of the care management of SSD/AHL patients, taking into account all positive and negative variations, the use of health resources that could result from the CI [41].

The BIA, which will be conducted using international and French guidelines, will include the predictable variation of context elements (e.g. demographic and epidemiological changes) [41, 42]. The social health insurance perspective will be taken and the time horizon will be 3 years.

The analysis will include three phases:

- An inventory of the care management of SSD/AHL patients,

- A care management model of these patients after the introduction of the new strategy (i.e. CI) to their care,

- The estimated cost for health insurance for these situations and the difference between the two strategies, to estimate the financial impact of the introduction of the new strategy in the treatment of SSD/AHL patients.

The introduction of the strategy based on the CI can change their own cost, but also have an impact on the size of the population (target and reached population), patterns of care performed prior to and after, the unit costs of resources mobilised in the context of strategies. The BIA should take these factors into account.

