**Discussion:**

The present study was designed to assess the efficiency of cochlear implantation in SSD/AHL. A favourable cost-utility ratio in this extended indication would strengthen the promising clinical results and justify a reimbursement by the health insurance. The efficiency of other options (CROS, BC) will also be described.

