In a prospective pilot study, Arndt et al. [25] showed that CI provided better performance than CROS or BAHAs previously tested by the same subjects, for several assessments of binaural hearing abilities. Several national multicentre trials have begun to compare hearing results after CI to those obtained with a CROS or BAHA system [30, 31]. These trials also assess the utility of the different treatments as a secondary objective, through their impact on quality of life with respect to their cost. The question of the cost/utility ratio of each treatment should indeed be raised because it is estimated that the global cost of cochlear implantation is approximately EUR 30,000 [32] while rehabilitation by CROS hearing aids or BAHA may cost EUR 2000 to EUR 3800. This gap between devices in terms of cost adds another substantial difference between CROS systems, BAHA and a cochlear implantation. Furthermore, treatment with cochlear implant involves a significant commitment on the patients’ part for the surgical procedure as well as for the rehabilitation programme; and although treatment by CROS hearing aids is not trivial, its consequences are much less significant.

All these differences between the possible treatments of SSD/AHL probably make cochlear implantation an option that is set apart from the others. Therefore in the recent consensus papers, it is not considered as an alternative among different options, but as a second-line treatment, in the event CROS or BAHA systems fail.

The present article describes a prospective multicentre randomised controlled trial initiated in France, which allows the subjects to choose their treatment option (observation, CROS, BAHA, or CI). The decision was made to randomise CI versus observation after a consecutive trial of CROS hearing aids and BAHA on a headband (Baha® or Ponto®) (see Fig. 1). Eventually, it aims to determine if CI is cost-effective in SSD/AHL, in subjects where CROS hearing aids and BAHA trials have failed.

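### The 6-month ICUR sets the one-off cost of a durable implant against half a year of benefit, so it cannot alone show whether CI is cost-effective

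*Protocol article*

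**What the plan says.** All references are to the protocol article.

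- **Endpoint and horizon.** Under Primary outcome measure, the aim is "to determine the incremental cost-utility ratio (ICUR) of cochlear implantation versus initial observation at 6 months". The cost-utility analysis relates costs to consequences "expressed in QALY gained, at 6 months between the two care management strategies".
- **Costs counted.** The same section includes "medication and medical device costs, especially the cost of the CI" among direct medical costs. It does not say that the device cost is spread over the device's life.
- **Size of the cost.** The Background states that "it is estimated that the global cost of cochlear implantation is approximately EUR 30,000".
- **Use of the result.** The last paragraph of the Background says the trial is meant to find out whether CI is cost-effective once CROS and BAHA trials have failed. The Discussion paragraph of the Abstract says: "A favourable cost-utility ratio in this extended indication would strengthen the promising clinical results and justify a reimbursement by the health insurance".
- **Other horizons.** The only longer one belongs to the budget impact analysis: "The social health insurance perspective will be taken and the time horizon will be 3 years". That analysis measures net costs to the insurer; QALYs are not part of its description.
- **Uncertainty analyses.** Statistical methods, data reporting and analysis describes deterministic variation of cost and utility inputs, a bootstrap interval for the ICUR and an acceptability curve. No other horizon is named there.
- **Control arm.** Under Study design and setting, observation-arm patients receive an implant after their 6-month evaluation.

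**The concern.** An implant is paid for once and used for years. The Background itself reports tinnitus relief lasting several years after the procedure. If the whole cost falls in the numerator while the denominator stops at 6 months, the size of the ratio reflects mainly where counting stopped.

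The result is intended for a reimbursement decision. A trial that met its own effect assumption could still report a ratio in the hundreds of thousands of euros per QALY, and that figure could be read as evidence against the device. The bootstrap and the acceptability curve, as described, concern the same ICUR and would not reveal the problem.

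**Working it through.** **1. What can be reproduced.** The article states no ICUR and no cost-effectiveness threshold. Its one related figure, 25 per arm for 0.8 SD at 5% alpha and 80% power (Population and sample size), reproduces: 2 × (1.96 + 0.84)² / 0.8² ≈ 24.5, rounded up to 25. The sample size is not in dispute.

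**2. Inputs.**
- Incremental cost C = EUR 30,000 (Background; approximate and cited). It is assumed to fall wholly inside the window.
- Horizon T = 0.5 year (Primary outcome measure).
- Utility gain Δu: not given, so assumed over a range.

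**3. Best case for the plan.** With the full gain from day 1, held to the end:

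ICUR = C / (Δu × T) = 30,000 / (0.5 × Δu) = 60,000 / Δu

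| Assumed Δu | ICUR at 6 months (EUR/QALY) |
|---|---|
| 0.10 | 600,000 |
| 0.20 | 300,000 |
| 0.40 | 150,000 |
| 1.0 | 60,000 |

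**4. Gain needed to meet an assumed threshold λ.** Δu = 30,000 / (0.5 × λ):
- λ = 30,000 needs 2.0
- λ = 50,000 needs 1.2
- λ = 60,000 needs 1.0
- λ = 100,000 needs 0.6

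**5. The plan's own effect size.** The article does not link its 0.8 SD to an EQ-5D utility SD. With an assumed SD of 0.15 to 0.30, the gain is 0.12 to 0.24 and the ICUR is EUR 500,000 to 250,000. The largest SD possible on a 0 to 1 scale is 0.5, which gives a gain of 0.40 and EUR 150,000. On an assumed scale from −0.5 to 1, the largest SD is 0.75, which gives a gain of 0.6 and EUR 100,000.

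**6. Effect of the horizon alone.** Constant gain, C = EUR 30,000, no later costs, undiscounted, in EUR/QALY:

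| Horizon | Δu = 0.10 | Δu = 0.20 |
|---|---|---|
| 0.5 year | 600,000 | 300,000 |
| 3 years | 100,000 | 50,000 |
| 10 years | 30,000 | 15,000 |
| 20 years | 15,000 | 7,500 |

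From 0.5 to 10 years the factor is 10 / 0.5 = 20. An assumed 2.5% discount rate changes the 10-year figures only to about 33,400 and 16,700.

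**7. Sensitivity to the other assumptions.** If the net cost were EUR 20,000, a gain of 0.20 would still give 20,000 / (0.5 × 0.20) = EUR 200,000. If the gain built up linearly over the 6 months, the QALYs would be 0.25 × Δu and every 6-month figure would double.

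**The case against.** **The horizon follows from the design.** Controls are implanted after 6 months for ethical reasons, so a randomised contrast cannot run longer, and the within-trial ICUR is a valid estimate of what it describes. This stands. It is why the 6-month ratio should be kept, and also why further randomised follow-up cannot supply the missing years.

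**The article is condensed.** An extrapolation may sit in the full protocol or analysis plan. This stands in part: one can say only that the article states none. But the article itself fixes the primary ratio at 6 months and attaches the cost-effectiveness and reimbursement claims to it.

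**The inputs are soft.** The EUR 30,000 is an approximate cited figure with no payer or period given, whereas the plan values care at insurer tariffs net of deductibles. This stands as a caveat; a net cost of EUR 20,000 does not change the conclusion.

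**The reimbursement sentence is conditional.** It speaks only of a favourable ratio and does not say that an unfavourable one would count against CI. That is correct. The broader claim rests on the aim stated in the Background.

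Two stronger readings are tempting but unsupported:

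- *A favourable ratio is arithmetically impossible.* The article gives no threshold and plans an acceptability curve over a range of them. At EUR 30,000, strict impossibility holds only below about EUR 60,000/QALY on a 0 to 1 utility scale. On an assumed scale from −0.5 to 1 it holds only below 60,000 / 1.5 = EUR 40,000. Above these limits the matter is one of plausibility.
- *The CI arm has only about 4 months of active device use.* That would follow if counting stopped 6 months after randomisation. Study design and setting instead places the CI-arm evaluation 6 months after activation. The calculation above therefore credits a full 6 months of benefit.

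**Conclusion.** The concern holds in a limited form. The 6-month ICUR is a legitimate within-trial result, but its size is governed largely by the horizon, and it cannot alone bear the conclusion the article attaches to it. At plausible utility gains of 0.10 to 0.20 it would be EUR 600,000 to 300,000/QALY. A favourable ratio is therefore very unlikely under assumed thresholds of EUR 30,000 to 100,000/QALY, while the same gain held for 10 years gives a ratio about 20 times lower.

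This rests on the article's EUR 30,000 falling within the window, on assumed utility gains and thresholds, and, for the longer horizons, on a constant gain with no later costs. The long-horizon figures show how much the horizon matters. They are not estimates of the true ratio and do not show that CI is cost-effective.

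**What to change.** 1. Keep the 6-month within-trial ICUR as the randomised result. State that it does not alone carry the cost-effectiveness or reimbursement conclusion, and bring the wording in the Abstract and Background into line.
2. Before analysis, pre-specify a model-based extrapolation of the cost-utility analysis beyond 6 months. Feed it with the trial's costs and utilities, and include discounting, later device costs, non-use and scenarios for how long the benefit persists. If the full protocol or analysis plan already contains such a model, refer to it and tie the conclusion to it.
3. Run the probabilistic sensitivity analysis and the acceptability curve on the extrapolated model as well as on the 6-month ICUR.

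Trial status reports inclusions complete and data controls ongoing, so this needs no new patients or visits. The cost is modelling work and plan wording. The real downside is that the long-term conclusion will depend on extrapolation assumptions that the randomised data cannot test, so those assumptions must be stated and varied openly.

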## Methods

### Study design and setting

This prospective multicentre national study combines two major steps:

- a prospective, descriptive observational cohort study, with a 6-month follow-up for SSD/AHL adult subjects treated by CROS, SSD/AHL subjects treated by an implanted bone conduction device (Baha or Ponto), and adult patients who decline all the options.

- and an open-label randomised controlled clinical trial for adults with SSD or AHL after failure of both CROS and BC systems, in two parallel groups: Observation for 6 months versus Cochlear implantation.

Participants are recruited in 7 tertiary referral centres in France. Once the inclusion/criteria are checked and the consent from the subject is obtained by one of the investigators, a reference evaluation is made for quality of life, binaural hearing performances (i.e. speech recognition in noise and horizontal localisation) and tinnitus severity. Then, CROS hearing aids and a BC device on a headband are successively tried by the subjects for three weeks each. The evaluation of quality of life, binaural hearing abilities, and tinnitus severity is repeated after the first trial (CROS) and the second trial (BC). At this point, the subject may choose the treatment he/she is willing to continue. If one of the trials (CROS or BC) is considered to be successful and the subject is willing to continue with the corresponding device, it is then provided and a new evaluation is performed 6 months later. If none of the trials is considered to be successful and the subject does not want any other treatment, then only a new evaluation is performed 6 months later. If none of the trials is considered to be successful and the subject wants treatment by cochlear implantation, the second major step of the study begins with the randomisation procedure.

Subjects who chose a cochlear implant are thus randomised between two arms: in the first one (“CI” arm), a cochlear implantation is performed within a month and a new evaluation on quality of life, binaural hearing performances, and tinnitus severity is planned 6 months after CI activation. Subjects of the second arm (“observation” arm) simply undergo the new evaluation 6 months after randomisation, without any intercurrent treatment for SSD/AHL. For obvious ethical reasons, subjects of the second arm benefit from a cochlear implantation after this 6-month evaluation.

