### Secondary outcome measures

All participants are asked to complete several quality of life questionnaires and hearing tests at inclusion and 6 months after their choice of the treatment (abstention, CROS hearing aids, BAHA, cochlear implantation). Pre/post treatment analyses will be carried out in each of these groups. Comparisons will be made in the group of subjects who chose a CI, randomised between immediate CI and initial observation.

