### Statistical methods, data reporting and analysis

Once the validity of the database is double-checked, descriptive analyses will be carried out for each treatment option (observation, CROS hearing aids, bone conduction device, cochlear implant). Quantitative variables will be described as means, standard deviations, and percentile distribution. The number and proportion of subjects will be used to describe categorical data.

Regarding the randomised controlled trial phase comparing CI versus observation, the analysis will be conducted on all subjects who were randomised on an intention-to-treat basis. For each outcome (quality of life, hearing performances indicators), the value measured at 6 months will be compared between the two groups using bivariate analyses (Student’s T test or Wilcoxon rank sum tests) and linear regressions adjusted for the baseline value.

For each intervention, we will assess the associations between changes in hearing performances and changes in quality of life. Data will be presented according to the Consolidated Standards of Reporting Trials (CONSORT) Statement [47, 48].

In order to test the robustness of the ICUR, deterministic and probabilistic sensitivity analyses will be conducted.

As part of the sensitivity analysis, we will determine the robustness of the results by testing the impact on the outcome of the variation of different cost and utility parameters [40]. Probabilistic sensitivity analysis, performed using the non-parametric bootstrap method, identified the uncertainty around the ICUR by estimating its confidence interval [49]. Moreover, a Cost-Utility Acceptability Curve (CUAC) will be built to summarise the impact of uncertainty on the ICUR in relation to possible values of the cost-effectiveness threshold [50].

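### As written, the primary ICUR uses the 6-month utility and an unadjusted difference of mean QALYs, so the QALY window and the baseline adjustment both need to be fixed

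*Protocol article*

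**What the plan says.** All references are to the protocol article.

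- **Primary outcome measure, definition.** "The utility is defined in this study as survival weighted by the quality of life of patients at 6 months (QALY". The section does not describe integration over time or a baseline term.
- **Primary outcome measure, ratio.** The analysis links costs to consequences "expressed in QALY gained, at 6 months between the two care management strategies". The ICUR "will be calculated as follows": mean cost (CI) minus mean cost (abstention), divided by mean QALY (CI) minus mean QALY (abstention). The only gloss is "Where ΔC and ΔU were increments of costs and utilities, respectively".
- **Secondary outcome measures.** Questionnaires are completed "at inclusion and 6 months after their choice of the treatment". Study design and setting adds quality-of-life evaluations after the CROS trial and after the BC trial. A pre-randomisation utility is therefore available.
- **Statistical methods, data reporting and analysis.** The 6-month value of each outcome (quality of life, hearing) is compared by simple tests and by "linear regressions adjusted for the baseline value". For the ICUR the section names only sensitivity analyses, a non-parametric bootstrap and an acceptability curve.
- **Study design and setting, timing.** In the CI arm, the evaluation of quality of life, binaural hearing and "tinnitus severity is planned 6 months after CI activation". Observation subjects "simply undergo the new evaluation 6 months after randomisation, without any intercurrent treatment for SSD/AHL".

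**The concern.** The ICUR is the primary outcome and is meant to inform reimbursement. Its denominator is a small number, so any proportional error in the QALY difference passes into the ratio in the same proportion.

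Two separate things are left loose.

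1. **The window.** Weighting a period by its closing utility credits the closing gain to every week of that period. In the CI arm the early weeks include the wait for surgery, the operation and the wait for activation.
2. **The contrast.** Quality of life as a stand-alone outcome is adjusted for baseline. The QALY difference that drives the primary result is not, as written. With about 25 subjects per arm, and randomisation stratified by centre only, a chance difference in baseline utility can be large relative to the planned effect.

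**Working it through.** **Plan's own figure.** Population and sample size gives 0.8 SD, alpha 5%, power 80% and 25 per arm. Two-sided normal approximation: n = 2 × (1.960 + 0.842)² / 0.8² = 24.5, so 25 per arm and 50 in total. This reproduces and is not in dispute.

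**A. Time before activation**

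Inputs from the article: surgery within a month of randomisation (Study design and setting) and activation about four weeks after surgery (Cochlear implant). Activation therefore falls about 1 to 2 months after randomisation, and the CI-arm evaluation at up to about 8 months. Let g be the utility gain at 6 months. The paths below are assumptions, because the article gives none. Each takes g as reached by month 6.

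Literal rule over 6 months from randomisation: 0.5 year × g = 0.50g.

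| Assumed path of the gain | Area over months 0 to 6 | 0.50g / area |
|---|---|---|
| Full step at month 1 | (5/12)g = 0.42g | 1.2 |
| Full step at month 2 | (4/12)g = 0.33g | 1.5 |
| Linear from randomisation | 0.5 × 0.5 × g = 0.25g | 2.0 |
| Flat to month 2, then linear to month 6 | 0.5 × (4/12)g = 0.17g | 3.0 |

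Illustration only: take the background figure of EUR 30,000 as the whole cost increment and assume g = 0.10. The ICUR per QALY is then:
- literal rule: 30,000 / 0.05 = EUR 600,000;
- step at month 2: 30,000 / 0.0333 = EUR 900,000;
- linear from randomisation: 30,000 / 0.025 = EUR 1,200,000.

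For assumed g of 0.05 to 0.15, the literal value runs from EUR 1.2m to 0.4m and the linear value from EUR 2.4m to 0.8m.

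Alternative reading: if the CI arm's six months start at activation, no pre-activation time is credited. Those weeks are instead left out of the CI arm's QALY. Follow-up then ends about 8 months after randomisation in the CI arm and 6 months after in the observation arm.

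**B. Chance baseline imbalance**

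In SD units with 25 per arm, the SE of the baseline difference is sqrt(2/25) = 0.283, and the 95% limit is 1.96 × 0.283 = 0.554. Let r be the baseline/6-month correlation, which is assumed.

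An imbalance d shifts the unadjusted end-value QALY difference by 0.5 × r × d. The planned effect is 0.5 × 0.8 = 0.4. The share is therefore r × d / 0.8.

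| r | d = one SE | d = 95% limit |
|---|---|---|
| 0.3 | 10.6% | 20.8% |
| 0.5 | 17.7% | 34.6% |
| 0.7 | 24.7% | 48.5% |

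**C. Would an area under the curve cure B?**

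No. A linear area without adjustment averages the baseline and 6-month values, so the shift is 0.5 × (1 + r)/2 × d, against a smaller gain of 0.25 × 0.8 = 0.2. At r = 0.5 and one SE: 0.5 × 0.75 × 0.283 = 0.106, and 0.106 / 0.2 = 53%, compared with 17.7% for the end value.

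**The case against.** **The horizon reading.** The reference to 6 months may mark the horizon over which QALYs accrue, not an end-value rule, since the neighbouring sentences use it that way. The article would then be silent on integration, which a health-economic plan may supply. This stands as a limit on the finding: the end-value rule is the literal reading but not the only one. It does not settle the window, because the two arms' clocks differ on either reading.

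**The formula is generic.** Adjusted means would fit it, and quality of life is adjusted elsewhere. This is partly right. The article does not forbid adjustment, but it attaches adjustment to the 6-month outcome values and names other methods for the ICUR.

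**Randomisation and the bootstrap already deal with imbalance.** Randomisation makes the imbalance a matter of chance, and the bootstrap carries its sampling uncertainty. Both points stand. The point estimate still contains whatever imbalance occurred, and the baseline information that could remove much of it goes unused.

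**The sizes are assumed.** This is correct. No utility path, gain or correlation is given in the article, and the planned sensitivity analyses may vary utility parameters.

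**A common window is not free.** This is also correct. No CI-arm evaluation is described at 6 months from randomisation, and observation subjects are implanted after their 6-month evaluation, so their window cannot be lengthened.

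**Conclusion.** The point holds as a defect of definition in the primary result. On the literal reading, the QALY gain is overstated about 1.2 to 1.5 times for a full step at activation, 2 times for a linear rise from randomisation, and 3 times for a linear rise from month 2 to month 6. If the CI clock starts at activation, the fault is unequal spans instead. Separately, for assumed correlations of 0.5 to 0.7, an imbalance at the 95% limit shifts the unadjusted end-value difference by 34.6% to 48.5% of the planned effect.

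A reader might infer more than the article supports:

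- *That the plan definitely uses the 6-month value alone.* The wording also allows accrual up to 6 months, and a fuller plan is not shown.
- *That CI would look at most, or exactly, twice as efficient as it is.* Two-fold belongs to one assumed path and is not a bound.
- *That implant benefit is counted before activation.* No such benefit exists then. The issue is the utility value assigned to that time.
- *That baseline imbalance biases the ICUR systematically.* Under 1:1 randomisation it is imprecision and conditional bias. It arises from the unadjusted means, not from the choice of the 6-month value.

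**What to change.** State the following in the analysis plan before the comparative analysis:

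1. **QALY.** Area under each subject's EQ-5D utility curve from randomisation over one common 6-month window in both arms.
2. **Baseline.** Name the pre-randomisation EQ-5D value used. Quality of life is evaluated at inclusion, after the CROS trial and after the BC trial, so the choice must be explicit.
3. **CI arm.** Interpolate utility to month 6 between the named baseline and the post-activation evaluation. Add a sensitivity analysis that holds utility flat until activation.
4. **Increment.** Estimate the incremental QALY by regression on arm and baseline EQ-5D. This must accompany the area under the curve, because an unadjusted area carries more of the imbalance (part C of the working).
5. **Uncertainty.** Recompute the adjusted increment in each bootstrap replicate, and use it for the ICUR and the acceptability curve.

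Cost: wording and programming only, with no new data. The article reports inclusions complete and data controls in progress. The price is a smaller, less favourable QALY gain than the literal rule would give, and an interpolation assumption in the CI arm.
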